### Ambulatory and Home Care Record (AHCR)

Out-of-hospital service use will be collected using a customised version of the AHCR [40]. The AHCR asks for the number of contacts in and out of the home with professionals or services, and informal care (hours per day) delivered by family or friends. It takes about 10 min to complete.

### Hospital Service Use Questionnaire (HSUQ)

Hospital use related to liver treatment (including drain insertion, drainage and complications) will be extracted by research staff from participant hospital records at the end of the study using a bespoke inhouse designed proforma distinguishing outpatient, accident and emergency (A&E), day case and overnight stays.

### Genetic and molecular analysis

Optional research blood samples (collected at baseline) and ascitic fluid samples (collected at baseline and four-weekly) will investigate potential biomarkers predicting outcomes in ACLD, such as infection and mortality. Consent for this optional aspect will be received separately. These biomarkers will include, but not be limited to, bacterial DNA, microbiota analysis, lipopolysaccharide binding protein, tumour necrosis factor, interleukin 6 and genetic testing. Removed LTADs will also be stored for biofilm analysis.

### Qualitative interviews

The aims of the qualitative component of the study are to explore the lived experience and acceptability of LVP and LTADs to patients, caregivers and HCPs.

Semi structured interviews with 30 patients (15 per group), 20 caregivers (10 per group) and 20 HCPs will be undertaken. Sample sizes are informed by the principles of information power [43]. Interviews will take place at different study timepoints ensuring patients have had at least one round of the intervention.

Information about the optional interview is included within study information sheets. HCPs will receive an information sheet solely about the interviews. All participating individuals will provide a separate, audio-recorded verbal consent for the interview.

Interview topic guides have been collaboratively developed with the PPI and clinical research team members. Topic guides for patients and informal caregivers will mirror each other, using broad prompts to ask about HRQoL and the experience of LTAD/LVP and decision-making at joining the study. The topic guide for HCPs will focus on the decision-making process for LTAD/LVP, and perceived impact, practical implications and implementation of the intervention. Completed interviews will be reviewed across the study to amend topic guides as necessary, incorporating any elements which seem to reoccur.

The interviews will be conducted by phone or video link and take between 15 and 45 min. To reduce patient burden, breaks will be allowed, and participants reminded they can stop the interview at any time. Interviews will be digitally recorded, transcribed and analysed.

### Communication skills training

Communication-skills training interventions can positively impact researchers involved in clinical trials [44–46]. Four communication workshops, open to all researchers involved in the trial, will be delivered during the recruitment period of the REDUCe2 study and address difficulties when discussing recruitment and topics around end-of-life, palliative care and death.

### Sample size calculation

The minimal clinically important difference (MCID) is the mean change in HRQoL scores for patients reporting a minimal yet perceptible change in health between the baseline and follow-up assessments [47]. In the ongoing LiverPal Study (one of the largest palliative trial in the USA [48], an MCID of 9 points on the FACT-Hep questionnaire was used [49]; and in a study assessing LTADs in cirrhosis,[50] an MCID of 10 points was chosen (SF-36 questionnaire[42]). While these studies show the use of MCID to inform sample size in palliative trials, neither of the tools selected are validated in ACLD. As we will be using the SFLDQoL [37], a sensitive and validated ACLD questionnaire, and to ensure a robust sample size, we have selected a MCID of 8 points.

In the earlier REDUCe trial [29], the pooled baseline mean across SFLDQoL domains (excluding sexual function) was 56.4 (SD = 26.1). With 93 participants in each group for the analysis, we will have 90% power for 5% significance to detect an adjusted difference in mean SFLDQoL scores of 8 points between the LTAD and LVP groups at the end of 3 months (effect size 0.31). This effect size falls within Cohen’s recommended cut offs for small (0.20) to moderate (0.50) effect size [51]. We assume a correlation between baseline and the 3 follow-up measurements of 0.48 which is the lower bound of the 95% confidence interval for the correlation from the feasibility data (point estimate 0.77) [29]. With an expected 40% attrition [29], we will recruit 310 participants in total for the trial. The sample size was calculated using Stata (version 17.0).

Following on from lessons learnt during the earlier feasibility study [29], to improve study retention, the protocol allows for proxy-scores to be collected on behalf of patients who may be too unwell to complete the questionnaires themselves. Secondly, appointment of consultees who can be approached in case of loss of capacity during the trial follow-up period will allow patients to be retained even in case of disease progression. Finally, to prevent recruitment late in their disease trajectory, we are providing communication skills training for researchers to facilitate difficult palliative care discussions.

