### Primary endpoint/outcome

The primary outcome is the difference in the overall mean of the disease-specific HRQoL scores between both groups assessed at 12 weeks using the Short Form Liver Disease Quality of Life (SFLDQoL) questionnaire [37].

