### Liver-specific HRQoL

This will be assessed at baseline and every four weeks using the SFLDQoL [37]. The SFLDQoL questionnaire is the only validated patient-reported outcome for ACLD and predicts mortality with accuracy comparable to MELD scores [9]. It includes 36 liver specific items across nine domains (distress, stigma, memory, symptoms and effects of liver disease, sleep, hopelessness, loneliness, and sexual function) scored on a 0–100 scale, where higher scores indicate better HRQoL. Due to low completion rates in the feasibility trial [29], sexual function data will be excluded from analysis but still recorded, should participants wish to answer. The questionnaire will be completed on paper or read out by researchers for patients who are too unwell. It takes 15–20 min to complete. The questionnaire also incorporates the 36-item Short Form Survey (SF-36) [42], which assesses generic HRQoL across eight domains, forming the two physical and mental component scores (PCS and MCS). The primary outcome only includes the liver-specific HRQoL measures and the PCS and MCS will be analysed separately. Caregivers or researchers can provide proxy scores when completing the questionnaire, if necessary. Although the primary outcome focuses on the SFLDQoL scores at three months, the questionnaire will be administered every four weeks to reduce the impact of missing data and improve the robustness of the statistical analysis model.

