**Fig. 4 Fig4:**
[figure not shown]
CONSORT diagram. Abbreviations: n number, LTAD long-term abdominal drain, LVP large volume paracentesis

For the primary outcome, the analysis will follow intention-to-treat principles and will be conducted using a linear mixed effects model. All patients randomised through Sealed Envelope will be included in the group to which they were allocated regardless of the outcome or clinical trajectory.

This model will include fixed effects: time point, sex, Child Pugh score, randomisation group, and an interaction between randomisation group and time point, while adjusting for baseline SFLDQoL scores. A random effect for participant will be included to handle the correlation between repeated measurements across the study period. The model parameters will be estimated using restricted maximum likelihood, and treatment differences between groups at each follow-up will be reported along with 95% confidence intervals and p-values. Secondary outcomes will similarly be analysed using mixed effects regression models suited to the type of outcome.

Subgroup analyses will aim to stratify data based on patient and site-level characteristics. Patient-level factors will include liver prognostic scores baseline ascitic fluid protein level, socioeconomic status, and the presence of informal caregivers. Site-level data will include prior experience with LTADs, availability of dedicated LVP units, cirrhosis nurses, Palliative care MDTs for ACLD, and Improving Quality in Liver Services (IQILS) programme accreditation. Subgroup analyses will allow for the identification of potential effect modifiers or predictors of outcomes and changes in HRQoL.

Only in the case of significant protocol deviations, agreed with the CI, will participants be excluded from the final analysis. In accordance with MORECare guidance for palliative trials, attrition due to mortality, illness, and withdrawal will be detailed for each group [53]. Missing quantitative data will be assumed to be missing not at random (MNAR) unless evidence suggests otherwise. Imputation models will be utilised followed by sensitivity analyses using plausible adjustments to explore the potential impact of missing data and MNAR assumptions on treatment outcomes (multiple imputation with delta adjustment).

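### The 90% power belongs to the average of three follow-up scores; for the 12-week difference named as primary, the stated inputs give about 66%

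*Protocol article*

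**What the plan says.** Four parts of the protocol article bear on this point.

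- **Primary endpoint/outcome** places the comparison at one visit: "The primary outcome is the difference in the overall mean of the disease-specific HRQoL scores between both groups assessed at 12 weeks".
- **Liver-specific HRQoL** confirms this and gives the other visits a supporting role, to limit the effect of missing data and strengthen the model: "Although the primary outcome focuses on the SFLDQoL scores at three months, the questionnaire will be administered every four weeks".
- **Statistical analysis** (under Data analysis) specifies a linear mixed model with "an interaction between randomisation group and time point, while adjusting for baseline SFLDQoL scores". It adds that "treatment differences between groups at each follow-up will be reported along with 95% confidence intervals and p-values". No effect averaged over visits is mentioned.
- **Sample size calculation** states: "With 93 participants in each group for the analysis, we will have 90% power for 5% significance to detect an adjusted difference" of 8 points "between the LTAD and LVP groups at the end of 3 months (effect size 0.31"). The SD is 26.1. On correlation it says: "We assume a correlation between baseline and the 3 follow-up measurements of 0.48". This value is the lower 95% confidence limit from the feasibility trial, where the point estimate was 0.77. With 40% attrition the target is 310 participants.

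**The concern.** The endpoint, the model and the wording of the power statement all describe a difference at week 12. The sample size section, however, brings three follow-up measurements into the calculation. A mean of three scores is less variable than a single score, so it needs far fewer participants. If 93 was computed for the mean, the 90% does not apply to the 12-week test.

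This matters most if the 12-week result is not significant. It would be read as coming from a trial with a one-in-ten chance of missing an 8-point effect. On the stated assumptions that chance is about one in three.

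The lower confidence limit of 0.48 is presented as a cautious choice. It is cautious for baseline adjustment. It is not cautious if the same value is also used between follow-up visits, because a low correlation there makes averaging look more efficient.

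**Working it through.** **Inputs from Sample size calculation:** difference 8; SD 26.1; effect size 0.31 (8/26.1 = 0.3065, rounded up); correlation 0.48; three follow-ups; 5% significance; 90% power; 40% attrition.

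**Assumptions not in the article:** a two-sided test, and a correlation between follow-up visits equal to the baseline-to-follow-up value.

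**Formula.** For baseline-adjusted analysis of the mean of *m* follow-ups with common correlation *r*:

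n per arm = 2 × (1.960 + 1.2816)² / ES² × F, where F = [1 + (m − 1)r]/m − r²

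and 2 × (1.960 + 1.2816)² = 21.015.

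**Step 1: reproduce the stated figure (m = 3, r = 0.48).**
- F = (1 + 2 × 0.48)/3 − 0.48² = 0.6533 − 0.2304 = 0.4229.
- ES = 0.31: 21.015/0.0961 × 0.4229 = 92.5, so **93**.
- ES = 8/26.1: 94.6, so 95; power at 93 is 89.5%.
- Attrition: 93/0.6 = 155 per arm, 310 in total, as stated.

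**Step 2: other designs at r = 0.48 (ES = 8/26.1).** None gives 93.

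| Design | n per arm |
|---|---|
| 12-week ANCOVA, two-sided | 173 |
| 12-week ANCOVA, one-sided | 141 |
| ANCOVA on mean of two follow-ups | 114 |
| Mean of three, no baseline adjustment | 147 |
| Change score, three follow-ups | 156 |
| Change score, one follow-up | 233 |
| Unadjusted t-test | 224 |

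**Step 3: the 12-week contrast (m = 1, r = 0.48).**
- F = 1 − 0.48² = 0.7696.
- Standard error at 93 per arm: 26.1 × √(2 × 0.7696/93) = 3.358.
- Power: Φ(8/3.358 − 1.960) = Φ(0.42) = **66.4%** (67.3% with ES = 0.31).
- Difference detectable with 90% power: 3.2416 × 3.358 = **10.9 points**.
- n for 90% power: 172.1, so 173 per arm (ES = 0.31: 168.3, so 169). After 40% attrition this means about 577 (or 564) recruited.

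**Step 4: dependence on the correlation (12 weeks, 93 per arm, ES = 8/26.1).**

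| r | Power |
|---|---|
| 0.48 | 66% |
| 0.60 | 74% |
| 0.70 | 83% |
| 0.77 | 91% |

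For 90% power, 1 − r² must equal 93 × 0.09395/21.015 = 0.416, so r must be about 0.76.

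**Step 5: credit for partial follow-up.** The mixed model also uses earlier scores from participants lost before week 12. The article gives no dropout pattern, so 134/114/93 per arm observed at weeks 4/8/12 is an illustration, and 155/155/93 is the most favourable case. The baseline correlation is 0.48 throughout.

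| Correlation between follow-ups | 134/114/93 | 155/155/93 |
|---|---|---|
| 0.48 | 68% | 69% |
| 0.60 | 70% | 72% |
| 0.77 | 74% | 78% |
| 0.90 | 78% | 83% |

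**Step 6: the averaged contrast if follow-ups correlate more strongly.** With baseline correlation 0.48 and an assumed 0.77 between follow-ups, F = (1 + 2 × 0.77)/3 − 0.2304 = 0.6163. Then n = 134.8 (ES = 0.31) or 137.8 (8/26.1), so 135 to 138 per arm. The figure of 93 needs the low value in both places.

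**The case against.** **The averaging is inferred.** The article does not say that the three scores were averaged and gives no correlation between follow-ups. The exact match also needs the rounded effect size; 8/26.1 gives 95. The full protocol, which is not shown, may name the formula. This stands as a caution. Even so, the article refers to three follow-ups, and at 0.48 no other design tried comes near 93. The 66% does not depend on the inference: it uses only the stated inputs and the stated endpoint.

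**The likelier correlation gives adequate power.** At 0.77, a 12-week ANCOVA needs 92 per arm (90 with ES = 0.31), close to 93, and power at 93 is about 91%. This limits the conclusion but does not rescue the claim, because the article says that 0.48 was the value assumed. The 12-week test reaches 90% only near the point estimate, so the intended margin is absent.

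**66% is a complete-case figure.** This is also fair. The planned model recovers some information from participants who drop out. But power stays at 83% or below across the range in Step 5. The higher values need follow-up correlations at which the averaged formula no longer gives 93. The 0.77 and other follow-up correlations used there are assumptions, since the article reports none.

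**Only a power figure is affected.** Type I error, the model and the confidence intervals are unaffected. That is correct, but this figure is the justification for the size of a definitive trial.

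**Conclusion.** The power statement is wrong for the endpoint it names. At a correlation of 0.48, SD 26.1 and 93 analysed per arm, a two-sided 5% test of an 8-point difference at 12 weeks has 66–67% power, which is 23 to 24 percentage points below the stated 90%. Crediting partial follow-up gives 68–69% with all correlations at 0.48, and at most about 83% with follow-up correlations up to 0.90.

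This does not show that the trial will be underpowered: if the baseline correlation is near 0.77, 12-week power is about 91%. It shows that the 90% claim and the cautious correlation cannot both hold for the 12-week contrast. The two-sided test is an assumption. That 93 came from averaging three follow-ups is an inference from the numerical match.

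**What to change.** Keep the 12-week difference as primary and correct the power statement in the protocol and SAP. It should say that 93 analysed per group gives about 66% power for 8 points at 12 weeks if the baseline correlation is 0.48, and about 91% if it is 0.77. If credit is taken for earlier visits in the mixed model, the assumed dropout pattern and correlation between follow-ups should be stated.

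The cost is a change of wording and a less favourable figure at the cautious correlation. An increase in recruitment is not proposed: it would mean about 577 participants instead of 310 to cover the lower limit, while the present size is adequate at the point estimate.

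The power statement and the primary contrast could also be matched by making the average over weeks 4, 8 and 12 primary, with week 12 as key secondary, before any unblinded look. I would not choose this. It changes the primary endpoint of an open-label trial that has recruited since November 2022 and whose central team knows recent allocations, and it abandons the stated focus on three months.

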### Harms and safety monitoring

Common Terminology Criteria of Adverse Events (CTCAE) version 4.03 [52] will be used to report any untoward medical occurrence in a trial participant, and its classification will depend on severity, seriousness, and relatedness to the intervention. Given the advanced nature of the illness, a high incidence of adverse events (AEs), including serious adverse events (SAEs) leading to patient death, is anticipated. While all adverse events and reactions must be documented in the electronic clinical case record form (eCRF), only potential Serious Adverse Reactions (SARs) require expedited reporting to the Brighton and Sussex Clinical Trials Unit (BSCTU) within 24 h. Any potential SARs will be immediately reviewed by the CI for relatedness and expectedness.

The Research Ethics Committee (REC) will be notified of any Suspected Unexpected Serious Adverse Reactions (SUSARs) and any urgent safety measures will be reported immediately to the REC and the University of Sussex (UoS), who is sponsoring the study. A list of the expected SARs that could be related to the insertion and management of LTADs along with anticipated harms that will be assessed systematically is included in Appendix 4. The CI will have ultimate responsibility for any reported SARs and SUSARs and will sign off any reports following a discussion with the local site PI. To minimise the risk of bias, given the open-label nature of the study, rates of adverse events will also be compared between the two groups irrespective of the assessed relatedness to the intervention. Adverse events (AE, SAE, AR, SAR) will be assessed through both direct and open questions at follow-up visits, and by reviewing fortnightly safety bloods and clinical records of patients at the end of the study. Anticipated harms of clinical interest will be reported irrespective of prevalence or seriousness. Other harms will only be reported if they are serious or above 5% prevalence.

### Data collection and management

Paper questionnaires and worksheets will be used for data collection across study sites. They will serve as source documents and transcribed onto the electronic data capture system MACRO™ [32]. The paper forms will be stored at study sites in fire-proof secure locked cupboards as per GCP requirement. All paper forms for the SFLDQoL and CRRS questionnaires will be scanned and sent to a central team at Sussex Health Outcomes Research and Education in Cancer (SHORE-C) who will conduct quality checks to ensure complete and accurate entry into the electronic database. The team will print their own copies of these questionnaires and store them in a locked office in a security-controlled building. These back-up copies will be confidentially destroyed once the study data has been published.

Additional source document verification for other questionnaires and clinical data will be carried out by the trial manager during on-site monitoring visits. Essential data will be kept for a minimum of five years, and research data kept in secure storage for ten years. Clinical outcomes will be self-reported and verified by research teams against linked medical records, with fortnightly bloods analysed by local site labs and reviewed by PIs.

The study will receive Research and Development confirmation of capacity and capability from all participating NHS Trust sites and expected to adhere to GCP guidelines, the approved study protocol, and any study specific SOPs. Participant data will also be entered onto the electronic data capture system. Participant data will be pseudoanonymised with identification numbers issued by the system. The SFLDQoL and CRRS questionnaires will be managed on a separate database housed on a secure UoS server. Data management will perform data checks on a regular basis for quality assurance.

### Data analysis

#### Statistical analysis

The flow of patients through the trial will be depicted in a Consolidated Standards of Reporting Trials (CONSORT) diagram (Fig. 4). Descriptive statistics will be used to summarise the data using means and standard deviations for normally distributed data, medians and interquartile ranges for skewed continuous variables, and frequencies and percentages for categorical variables.

**Fig. 4 Fig4:**
[figure not shown]
CONSORT diagram. Abbreviations: n number, LTAD long-term abdominal drain, LVP large volume paracentesis

For the primary outcome, the analysis will follow intention-to-treat principles and will be conducted using a linear mixed effects model. All patients randomised through Sealed Envelope will be included in the group to which they were allocated regardless of the outcome or clinical trajectory.

This model will include fixed effects: time point, sex, Child Pugh score, randomisation group, and an interaction between randomisation group and time point, while adjusting for baseline SFLDQoL scores. A random effect for participant will be included to handle the correlation between repeated measurements across the study period. The model parameters will be estimated using restricted maximum likelihood, and treatment differences between groups at each follow-up will be reported along with 95% confidence intervals and p-values. Secondary outcomes will similarly be analysed using mixed effects regression models suited to the type of outcome.

Subgroup analyses will aim to stratify data based on patient and site-level characteristics. Patient-level factors will include liver prognostic scores baseline ascitic fluid protein level, socioeconomic status, and the presence of informal caregivers. Site-level data will include prior experience with LTADs, availability of dedicated LVP units, cirrhosis nurses, Palliative care MDTs for ACLD, and Improving Quality in Liver Services (IQILS) programme accreditation. Subgroup analyses will allow for the identification of potential effect modifiers or predictors of outcomes and changes in HRQoL.

Only in the case of significant protocol deviations, agreed with the CI, will participants be excluded from the final analysis. In accordance with MORECare guidance for palliative trials, attrition due to mortality, illness, and withdrawal will be detailed for each group [53]. Missing quantitative data will be assumed to be missing not at random (MNAR) unless evidence suggests otherwise. Imputation models will be utilised followed by sensitivity analyses using plausible adjustments to explore the potential impact of missing data and MNAR assumptions on treatment outcomes (multiple imputation with delta adjustment).

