Palliative long-term abdominal drains (LTADs) are standard of care in malignant ascites [22–25]. These tunneled drains allow community nurses or caregivers to drain small volumes of ascitic fluid at home. Compared to LVP, LTADs have the potential advantage of improving HRQoL by reducing ascites-related-hospitalisation and improving symptom control and could also be cost effective [22–25]. Their use in ACLD, however, has been limited due to the scarcity of evidence, largely due to a perceived infection risk, especially peritonitis, and uncertainty regarding community management [26]. However, a recent systematic review [27], case series [28], as well as an earlier feasibility trial [29], have provided preliminary evidence of acceptability, safety, efficacy, and cost-effectiveness of LTADs in ACLD. Currently, pending definitive evidence, the National Institute for Health and Care Excellence (NICE) recommends the use of LTADs in ACLD only in the context of special arrangements (i.e. in research or closely audited practice) [30].

Delivering palliative interventional trials in ACLD can be challenging [31]. However, the lack of evidence-based interventions is a factor in the inequity of palliative care provision for patients with ACLD, hence the need for this trial.

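### Cumulative peritonitis incidence is committed to mixed effects regression, a family that does not itself give a cumulative incidence, and the text does not say how death or withdrawal enters

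*Protocol article*

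**What the plan says.** The Secondary endpoints/outcomes section lists cumulative peritonitis incidence first, and infection, peritonitis in particular, also heads the Secondary objectives. The Background explains the interest: use of these drains in cirrhosis has been limited, "largely due to a perceived infection risk, especially peritonitis".

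The Statistical analysis section says that the primary analysis "will be conducted using a linear mixed effects model", with a random effect for participant to account for repeated measurements. It continues: "Secondary outcomes will similarly be analysed using mixed effects regression models suited to the type of outcome". Apart from percentages as descriptive statistics for categorical variables, the shown text gives no other method for the peritonitis outcome.

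On loss and death:
- Sample size calculation: "With an expected 40% attrition [29], we will recruit 310 participants in total for the trial".
- Statistical analysis: "attrition due to mortality, illness, and withdrawal will be detailed for each group", and "Missing quantitative data will be assumed to be missing not at random (MNAR) unless evidence suggests otherwise", followed by multiple imputation with delta adjustment.
- Harms and safety monitoring: "a high incidence of adverse events (AEs), including serious adverse events (SAEs) leading to patient death, is anticipated". Adverse event rates are also to be compared between groups whatever their judged relatedness, and clinical records are to be reviewed at the end of the study.
- Data collection and management: self-reported clinical outcomes are checked against linked medical records.
- Health economic analysis: the authors accept that time in the study will vary between patients.

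**The concern.** Peritonitis is the main safety question about the drain. A cumulative incidence is the probability of a first event by a fixed time, here 12 weeks, and each patient contributes one value. A participant random effect then has no repeated measurement to model. If the model is instead fitted to fortnightly yes/no records, it estimates odds per visit among patients still alive and under observation, which is a different quantity from the endpoint named.

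Many deaths are expected. A patient who dies without peritonitis can no longer develop it, so death is a competing event. A patient whose follow-up ends early has an unknown later history, so withdrawal is censoring. The text assigns neither role for this outcome. The imputation strategy does not fill the gap, because imputing peritonitis after death has no meaning. The trial is open-label, so exits could differ by arm. If they did, and if withdrawn patients were counted as free of infection, a real excess could be diluted or an apparent difference produced.

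**Working it through.** **The plan's own figure.** The plan gives no figure for peritonitis. The 40% attrition belongs to the sample size for the quality-of-life questionnaire, and it reproduces: 93 / (1 − 0.40) = 155 per arm, 310 in total. It is therefore an all-cause allowance for the questionnaire analysis.

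**Inputs.** The documents give no peritonitis, death or withdrawal rates, so all rates below are assumptions. Each is a net 12-week risk p, converted to a constant hazard by −ln(1 − p). Write l for peritonitis, d for death and w for withdrawal.

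**Formulas.**
- Cumulative incidence with death competing: CIF = l/(l+d) × [1 − exp(−(l+d))].
- Crude proportion with withdrawn patients counted as event-free: l/(l+d+w) × [1 − exp(−(l+d+w))].
- Per-visit probability over six fortnightly intervals among patients still at risk: l/(l+d+w) × [1 − exp(−(l+d+w)/6)].

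Hazards: 10% → 0.1054; 15% → 0.1625; 20% → 0.2231; 25% → 0.2877; 30% → 0.3567.

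**A. Equal hazards, equal loss.** Peritonitis 10%, death 20%, withdrawal 25% in both arms. Attrition is 1 − 0.80 × 0.75 = 40%.
- CIF = 0.1054/0.3285 × (1 − e^−0.3285) = 9.0%.
- Crude = 0.1054/0.6162 × (1 − e^−0.6162) = 7.9%.
- The crude level is about 12% too low, but the ratio between arms is 1.00 either way.

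**B. True excess, very unequal loss.** Peritonitis 15% with 30% death and 30% withdrawal, against 10% with 10% and 10%. Attrition is 1 − 0.70 × 0.70 = 51% against 1 − 0.90 × 0.90 = 19%.
- Cause-specific hazard ratio = 0.1625/0.1054 = 1.54.
- CIF: 0.1625/0.5192 × (1 − e^−0.5192) = 12.7%, against 0.1054/0.2107 × (1 − e^−0.2107) = 9.5%. Ratio 1.33.
- Crude: 0.1625/0.8759 × (1 − e^−0.8759) = 10.8%, against 0.1054/0.3161 × (1 − e^−0.3161) = 9.0%. Ratio 1.20.
- Per-visit: 0.02520 against 0.01711. Odds ratio 1.49.

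**C. Equal hazards, unequal loss.** Peritonitis 10% in both arms, exits 20% and 25% against 10% and 10%.
- Crude: 7.9% against 9.0%, ratio 0.87.
- CIF: 9.0% against 9.5%, ratio 0.945.
- Per-visit: 0.01669 against 0.01711. Odds ratio 0.98, against a true hazard ratio of 1.00.
- Of the 13% crude reduction, 0.055/0.129, or about 40%, remains in the CIF. It reflects competing mortality and is not an artefact.

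**D. Full tracing.** Setting w = 0 makes the crude formula identical to the CIF. If records are followed for everyone randomised, the simple proportion estimates the cumulative incidence without this bias.

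**The case against.** The strongest objection is that the distortion shown above belongs to a crude proportion, and the plan does not say it will compare crude proportions. A per-visit model in which patients leave the risk set at first peritonitis is close to a discrete-time hazard model. Its odds ratios, 1.49 and 0.98, lie near the true hazard ratios of 1.54 and 1.00. This stands: for that form of the model, unequal exits do little harm to the relative comparison. What it yields is still not a cumulative incidence, and the text does not say that this form is meant.

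A reader might infer that peritonitis goes into the same model as the quality-of-life scores and that death and withdrawal are ignored in about 40% of patients. The documents do not support that reading. The sentence lets the model vary with the outcome, which leaves room for a logistic, count or frailty model, or for a random effect other than participant. Attrition by cause is to be reported per group, missing data get sensitivity analyses, and adverse event rates are compared between arms. The 40% sizes the questionnaire analysis. Peritonitis can be found in the records of patients who complete no questionnaire.

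It is also fair to say that a journal article may leave the choice of method to the analysis plan. Silence would be no finding. Here, however, the text names a model family for every secondary outcome, so an analysis plan using a cumulative-incidence method would depart from it.

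**Conclusion.** The point holds in limited form. The protocol assigns its main safety endpoint to a model family that does not itself deliver the quantity named, and leaves open how death and withdrawal enter. A biased arm comparison is possible but not demonstrated. It needs arm-different loss to peritonitis ascertainment together with an analysis that treats lost patients as event-free. With equal loss or full record tracing it is essentially nil. Scenario B, where the crude ratio of 1.20 compares with a CIF ratio of 1.33, rests on assumed rates, constant hazards and an imbalance of 51% against 19% chosen to show the mechanism. Nothing in the documents predicts such an imbalance. The change is still worth making, because the better method is standard, cheap and largely served by data already planned.

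**What to change.** Restrict the mixed-model sentence to the repeated scores. For peritonitis, state that time from randomisation to first episode will be analysed, reporting:
- the Aalen-Johansen 12-week cumulative incidence by arm, with death as a competing event and censoring when access to records is withdrawn;
- the risk difference with 95% CI;
- a cause-specific hazard ratio adjusted for sex and Child-Pugh score, the two minimisation factors.

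Report the incidence and the hazard ratio together, since scenario C shows that differing mortality alone can move the former. State that the planned record review will be used to ascertain peritonitis in patients who stop visits, and that events after death will not be imputed.

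The cost is a sentence or two in the protocol or analysis plan, a little more analysis work, and dates of first peritonitis, death and withdrawal in the case record form. No extra patients or visits are needed.
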